### Statistics

All analysis will be performed using SPSS Statistical Software (IBM SPSS Statistics for Windows, Version 21.0. Armonk, NY: IBM Corp.). Continuous variables will be presented as mean ± SD and categorical variables as frequencies. Differences between the both groups at baseline will be evaluated by unpaired *t* test or the Mann–Whitney test for comparison of continuous variables. The Chi square test or Fisher’s exact test will be employed to compare categorical variables. The change from baseline to 12-weeks follow-up in the both groups will be evaluated using the paired *t* test for continuous variables. Pearson’s correlation will be used to assess the relationship between HbA1c and RHI and AIx, after confirmation of similarity between groups in respect to demographic data (age, gender, GFR, and comorbidities: hypertension and dyslipidemia) and HbA1c targets after 12 weeks of considered treatment. Thus, the Pearson’s correlation obtained will be potentially consequent to distinct therapeutic responses. For all analysis, a 2-sided *P* < 0.05 will be considered statistically significant.

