**Results:**

The study started in December 2013 and patient recruitment is programed until October 2015. The expected results are that vildagliptin will improve the endothelial function in patients with T2DM and hypertension compared to glibenclamide treatment, independently of glycemic control.

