## Outcomes and outcome adjudication

Change in the RHI from baseline after 12 weeks of vildagliptin vs. glibenclamide treatment.Change in the central blood pressure from baseline to after 12 weeks of vildagliptin vs. glibenclamide treatment.

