## Statistical considerations

### Sample size and power calculations

The site http://www.lee.dante.br-pesquisa was used to estimate the sample size, considering a 30 % change in the RHI between treatment groups as clinically relevant. Assuming a standard deviation of 0.3 would require a total of 21 subjects to detect a 30 % change in the RHI with a power of 80 % at a significant level of 0.05. However, considering a potential 20 % of drop-out or lost to follow-up rate, a total of 50 patients (25 for each group) will be considered.

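### The article names only a within-arm paired test for the 12-week change, although its outcomes, sample size and expected conclusion are all contrasts of vildagliptin with glibenclamide

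*Protocol article*

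**What the plan says.** The question is comparative in three places of the protocol article:

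- *Outcomes and outcome adjudication* gives the first outcome as "Change in the RHI from baseline after 12 weeks of vildagliptin vs. glibenclamide treatment". Central blood pressure is worded the same way.
- *Sample size and power calculations* takes a 30% "change in the RHI between treatment groups as clinically relevant", with an SD of 0.3, 80% power and a 0.05 level.
- The abstract's *Results* expects vildagliptin to improve endothelial function "compared to glibenclamide treatment, independently of glycemic control". *Results/discussion* repeats the expectation of superiority.

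The *Statistics* section then assigns methods:

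- Change over time: the sentence that opens "The change from baseline to 12-weeks follow-up in the both groups will be evaluated using the paired" goes on to name Student's test for this purpose.
- Comparability at entry: here the wording is "Differences between the both groups at baseline will be evaluated by unpaired", and the method is Student's test with Mann–Whitney as its alternative.
- Categorical data are left to chi square or Fisher tests.
- HbA1c, RHI and AIx are linked by Pearson correlations, on condition that the two arms first prove similar in demographic features and HbA1c targets.

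All tests are two-sided at 0.05.

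**The concern.** A paired *t* test sets each patient against his or her own baseline. It asks whether the mean change in one arm differs from zero, not whether the two arms differ. Randomisation protects the contrast between arms. A change inside one arm also contains whatever happens to both.

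The document makes some shared change plausible. Metformin is adjusted to glycaemic control in both arms, and *Results/discussion* says that both drugs may improve glycaemic control and that hyperglycaemia impairs the endothelium. Renin-angiotensin blockers are prescribed to everyone at screening. Table 2 puts the baseline vascular tests at Visit 1, after that, so only an effect still developing after Visit 1 would enter the measured change.

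At stake is the main comparative claim. If the section is followed literally, the trial reports two within-arm p values and no estimate, interval or test of the difference it was sized to detect. The comparison method could then be chosen after the results are known.

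**Working it through.** **1. Match each named method to the outcome.**

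| Method in *Statistics* | What it compares | Tests the difference in 12-week change between arms? |
|---|---|---|
| Unpaired *t* / Mann–Whitney | Arms, at baseline | No |
| Chi square / Fisher | Categorical variables | No: RHI change and central blood pressure change are continuous |
| Paired *t* | Week 12 against own baseline | No: within arm |
| Pearson correlation | HbA1c with RHI and AIx | No: association between two measurements |

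No row addresses the stated outcomes. This step needs no numerical assumption.

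**2. The plan's own figure.** For two means, n per arm = 2(1.960 + 0.842)² × SD²/Δ² = 15.70 × SD²/Δ². The article gives a percentage effect and no baseline RHI, so Δ is not fixed.

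- Δ = 0.30, SD = 0.3: 15.7, so 16 per arm (32 in total).
- Δ = 30% of the 1.68 cut-off = 0.504: 15.70 × (0.3/0.504)² = 5.6, so 6 per arm (12 in total).

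Neither gives the stated total of 21. That is a separate matter and nothing below rests on it. What matters here is that the 80% is stated for a between-group change.

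**3. What inference from two paired tests would do.** The rule examined is: claim a difference if vildagliptin improves significantly and glibenclamide does not. The article does not state this rule.

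Inputs:
- 20 completers per arm = 25 × (1 − 0.20), from the sample-size section.
- SD of change 0.3. This is an assumption: the article does not say whether its SD is of RHI or of its change.
- Shared change *d* in both arms: unknown, taken from 0 to 0.30.
- True difference 0.273 for the power side. This is also an assumption: it is the value at which an unpaired *t* test with 20 per arm has 80% power, so the 80% comparator holds by construction.

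Let p(*d*) be the chance that one arm's paired *t* test shows significant improvement: P(T > 2.093), with T noncentral *t* on 19 degrees of freedom and noncentrality *d*√20/0.3.

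- False claim for vildagliptin when the true changes are equal: p(*d*)[1 − p(*d*)].
- Success when vildagliptin is better by 0.273: p(*d* + 0.273)[1 − p(*d*)].

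Worked line, *d* = 0.15: noncentrality 0.15 × 4.472/0.3 = 2.236 and p = 0.5645. False claim: 0.5645 × 0.4355 = 24.6%. Success: p(0.423) is 1.000 to three decimals, so 1.000 × 0.4355 = 43.5% (44% by simulation).

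| Shared change *d* | p(*d*) | False claim for vildagliptin | Success, true difference 0.273 |
|---|---|---|---|
| 0 | 0.025 | 2.4% | 94.7% |
| 0.05 | 0.105 | 9.4% | 89.0% |
| 0.08 | 0.204 | 16.2% | 79.5% |
| 0.10 | 0.293 | 20.7% | 70.6% |
| 0.15 | 0.565 | 24.6% | 43.5% |
| 0.20 | 0.807 | 15.6% | 19.3% |
| 0.30 | 0.989 | 1.1% | 1.1% |
| Between-arm *t* test, any *d* | – | 2.5% | 80.1% |

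The product p(1 − p) peaks at 0.25 when p = 0.5, here at *d* of about 0.14. The 25% ceiling does not depend on the SD; only its location does.

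**4. Would a between-arm test work at the planned size?** In simulation (100,000 trials, 20 per arm, equal true change), an unpaired *t* test on change had a two-sided type I error of 5.0%. Its power for a difference of 0.30 with SD 0.3 is 86.9%. It is feasible if those assumptions hold.

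**The case against.** The strongest reply is that this is a condensed article. A fuller protocol or analysis plan, not shown here, may name a between-arm test, and the article never says that significance in one arm only would be read as a drug difference.

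Much of this stands. A reader might infer that the comparison will never be tested, or that contrasting two p values is the investigators' only route to a claim. The text supports neither. It writes no such rule, and it also describes a comparative reading of the Pearson correlations as reflecting distinct therapeutic responses, although that is not a test of the treatment effect. The error rates in the table are therefore conditional on an assumed inference.

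Three other stronger readings also fail.

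- The false-claim rate is not uniformly high. It is near or below 2.5% at both ends of the range, and no figure in the document points to the middle.
- The within-arm rule does not always lose power. With a shared change of 0 or 0.05 it succeeds more often than the between-arm test.
- Selection-driven regression to the mean in RHI is not to be expected, because Table 1 does not select on RHI. The 1.68 threshold defines dysfunction and is not an entry criterion.

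What the reply does not remove is the mismatch. The article does not merely leave the test to another document. It assigns a test to the change from baseline, and that test cannot answer the question posed by its outcomes. The unpaired test is expressly attached to baseline, so it cannot be read as covering follow-up.

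**Conclusion.** The concern holds in this form: a within-arm test is named for a between-arm outcome, and no method in *Statistics* compares the change in RHI or central blood pressure between arms. That conclusion rests on the text alone. It follows that the stated 80% power does not describe the paired tests.

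The numerical consequence is conditional. With 20 completers per arm, an assumed SD of change of 0.3 and an inference from significance in the vildagliptin arm only, false claims for vildagliptin range from about 1% to 25% over shared changes of 0 to 0.30, against 2.5%. With an assumed true difference of 0.273, success ranges from about 95% to 1%, against 80%. The shared change is unknown, so neither rate is controlled under that inference. This does not show that the trial will reach a wrong conclusion. The point should be corrected because the main comparison has no named test.

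**What to change.** In *Statistics*, name a between-arm comparison as the primary analysis of the 12-week change in RHI, and the same for central blood pressure. The preferred form is ANCOVA of the week-12 value on treatment, with the baseline value as covariate, reporting the adjusted difference, its 95% confidence interval and the two-sided p value. An unpaired *t* test on change is the minimum that closes the gap.

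ANCOVA is preferred for precision. With SD σ at each visit and baseline-to-follow-up correlation ρ, the outcome variance is σ²(1 − ρ²), against 2σ²(1 − ρ) for change. At an assumed ρ of 0.5 that is 0.75σ² against 1.00σ².

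Keep the paired *t* tests as descriptive and state that no treatment claim rests on them. Analysing RHI on the log scale and extending the model to AIx are optional.

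The cost is one paragraph, written before the data are locked. Baseline values are already collected in both arms, SPSS fits the model, and no extra patients or visits are needed.

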## Randomization and follow-up

After screening for eligibility, 50 individuals will be submitted to an evaluation of endothelial function using the Endo-PAT 2000 device and measurement of the arterial stiffness by applanation tonometry of radial artery. Subsequently, they will be randomly allocated to the two arms of the study: Group 1 will receive vildagliptin (100 mg/day b.i.d.) added-on to metformin (500–2550 mg/day according to glycemic control) and Group 2 will receive glibenclamide (5–20 mg/day according to glycemic control) added-on to metformin (500–2550 mg/day according to glycemic control). Blood samples will be collected after 12-h overnight fasting at screening visit and then after 12 weeks of treatment with vildagliptin (Group 1) or glibenclamide (Group 2). Renin-angiotensin system blockers will be prescribed to all subjects at the screening visit and all other antihypertensive drugs will be maintained. Subjects will have three return consultations. The first will be to randomize patients to Group 1 or 2 and they will be evaluated after four and 12 weeks. Compliance will be monitored by pill counts at the second and last visits. The glycemic control will be evaluated by glycated hemoglobin and fasting glucose. Adverse events will be evaluated on the basis of spontaneous reports and interviews by the investigator. Considering side effects and safety, nausea, upper abdominal pain and flatulence are expected, although uncommon, while taking vildagliptin. The most frequent side effect of glibenclamide is hypoglycemic events. Changes in blood count, renal function, and liver function are not expected with either treatment.

Table 2 shows a summary of key practical aspects of the study with all follow-up visits and requested exams.

**Table 2 Tab2:** Key practical aspects of the study with all the clinical visits and the requested exams

Visits	Screening	Visit 1	Visit 2	Visit 3
Weeks	−1	1	4	12
Informed consent	X			
Inclusion and exclusion criteria	X	X		
Medical history	X			
Medical evaluation/physical examination	X	X	X	X
Randomization		X		
Pregnancy test	X			
Creatinine	X			X
Fasting glucose	X		X	X
Ultrasensitive C-reactive protein	X			X
Total cholesterol	X			X
High-density lipoprotein cholesterol	X			X
Triglycerides	X			X
Glycated hemoglobin	X			X
Alanine aminotransferase	X			X
Microalbuminuria	X			X
Ambulatory blood pressure monitoring		X		X
Treadmill test	X			
Determination of the central aortic pressure and vascular stiffness markers		X		X

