## Results/discussion

The study has started in December 2013 and patient recruitment is programed until October 2015. It is expected that vildagliptin will improve the endothelial function in patients with T2DM and hypertension more than glibenclamide treatment. Hyperglycemia causes endothelial dysfunction because it reduces the bioavailability of endothelium-derived nitric oxide (NO). Although the main action of GLP-1 is to increase glucose-stimulated insulin secretion from pancreatic beta cells, there is also evidence of physiological signaling from GLP-1 in endothelial and vascular smooth muscle cells. Thus, GLP-1 has vasodilator actions mediated by a specific GLP-1 receptor in the vascular endothelium and may improve endothelial function in animals and humans [15–17], independently of its effect on glycemic control.

Arterial stiffness is recognized as another cardiovascular risk marker [32]. Patients with both HT and DM exhibit higher arterial stiffness compared to those with either DM or HT alone [33]. Applanation tonometry estimates arterial compliance and the central blood pressure and is used to assess arterial stiffness [42, 43]. Evidence shows that the central blood pressure is more relevant to cardiovascular outcomes than the peripheral BP [44–46]. On the other hand, Endo-PAT, a non-invasive method, evaluates the vascular vasodilator propriety and, consequently, endothelial function. Both hypoglycemic drugs, vildagliptin and glibenclamide, may improve glycemic control. However, only vildagliptin and other DPP-4 inhibitors have provided beneficial effects of the endothelium [22, 23].

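### The 12-week change is assigned to a within-arm paired t test, so no named test compares vildagliptin with glibenclamide on either outcome

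*Protocol article*

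**What the plan says.** All references are to the Protocol article.

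- **Outcomes and outcome adjudication** defines two outcomes, each as a contrast between the drugs: "Change in the RHI from baseline after 12 weeks of vildagliptin vs. glibenclamide treatment" and "Change in the central blood pressure from baseline to after 12 weeks of vildagliptin vs. glibenclamide treatment".
- **Sample size and power calculations** sizes the trial on a 30% "change in the RHI between treatment groups as clinically relevant".
- **Results/discussion** states the expected finding comparatively: "It is expected that vildagliptin will improve the endothelial function in patients with T2DM and hypertension more than glibenclamide treatment".
- **Statistics** names the tests. For the unpaired t and Mann–Whitney tests: "Differences between the both groups at baseline will be evaluated by unpaired". For follow-up: "The change from baseline to 12-weeks follow-up in the both groups will be evaluated using the paired" t test. Chi square and Fisher's exact tests are for categorical variables. Pearson's correlation relates HbA1c to RHI and AIx, "after confirmation of similarity between groups in respect to demographic data" and in HbA1c targets at 12 weeks.

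**The concern.** The aim, the outcomes and the sample size all concern a difference between two drugs. The test given to the 12-week change answers another question: whether each arm moved from its own baseline. Patients in parallel arms are not paired with each other, so a paired t test cannot be run across the arms.

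A within-arm test also credits to the study drug anything that changes in both arms. The article itself offers candidates:

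- Results/discussion says that hyperglycaemia impairs endothelial function and that both drugs may improve glycaemic control.
- Metformin is adjusted to glycaemic control in both arms.
- Time trends are possible.
- "Renin-angiotensin system blockers will be prescribed to all subjects at the screening visit", shortly before the Visit 1 vascular measurements. This is not a fault: both arms get it before randomisation, so a comparison between arms is not biased by it.

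If the plan is followed, the only way to judge the drugs against each other is to set two paired p values side by side. A trial could then report that vildagliptin beats glibenclamide when the arms do not differ, or miss a real difference because both arms improved.

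**Working it through.** **Step 1. Is there a named test for the stated outcomes?** The tests in the Statistics section, taken in turn:

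| Test | Use given to it | Compares 12-week change between arms? |
|---|---|---|
| Unpaired t, Mann–Whitney | Differences at baseline | No |
| Chi square, Fisher | Categorical variables | No; both outcomes are continuous |
| Paired t | Change from baseline to week 12 | No; within each arm only |
| Pearson | HbA1c with RHI and AIx | No |

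The similarity check on 12-week HbA1c targets does touch follow-up, but only as a condition for the correlation. No test of the outcome contrast is named.

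**Step 2. The plan's own figure.** The stated total of 21 subjects cannot be uniquely reproduced, because the baseline RHI that the 30% refers to is not given. It does not bear on which test is named.

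**Step 3. What two paired tests give when the arms do not differ.**

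Inputs from the article: 25 per arm; 20 per arm after the 20% drop-out allowance; two-sided 0.05; SD 0.3. Assumptions: normally distributed changes, and a change c shared by both arms, in units of the SD of change. The article gives no value for c, so it is varied. If the SD of 0.3 is taken as the SD of RHI change (the article does not say which SD it is), c = 0.05 to 0.4 is 0.015 to 0.12 RHI units.

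For one arm the paired t statistic is noncentral t with n − 1 degrees of freedom and noncentrality c√n. Let q be the probability of significance in either direction and u the probability of significant improvement. The arms are independent, so:

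- P(vildagliptin significantly better, glibenclamide not significant) = u(1 − q)
- P(exactly one arm significant) = 2q(1 − q)

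Example: n = 25, c = 0.2. Noncentrality = 0.2 × 5 = 1.0 and the critical value is 2.064, so q = 0.161 and u = 0.159. Then u(1 − q) = 0.159 × 0.839 = 0.133 and 2q(1 − q) = 2 × 0.161 × 0.839 = 0.270.

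| c | n = 25: q | u(1 − q) | 2q(1 − q) | n = 20: q | u(1 − q) | 2q(1 − q) |
|---|---|---|---|---|---|---|
| 0 | 5.0% | 2.4% | 9.5% | 5.0% | 2.4% | 9.5% |
| 0.05 | 5.7% | 4.0% | 10.7% | 5.5% | 3.8% | 10.4% |
| 0.1 | 7.7% | 6.4% | 14% | 7.1% | 5.8% | 13% |
| 0.2 | 16% | 13% | 27% | 14% | 12% | 23% |
| 0.4 | 48% | 25% | 50% | 40% | 24% | 48% |

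**Step 4. The same setting with a between-arm test.** In 20,000 simulated trials per case (n = 25 and 20; baseline correlation 0.3, 0.5 and 0.7; c = 0, 0.2 and 0.4), the unpaired t test on change and ANCOVA each rejected in 4.7% to 5.2%. The shared change cancels.

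**Step 5. A real difference.** Assume a true difference of 0.8 SD (0.8 × 0.3 = 0.24 RHI units). The vildagliptin-only pattern has probability u at c + 0.8 multiplied by (1 − q) at c:

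| n per arm | c = 0 | c = 0.2 | c = 0.4 | Power, unpaired t on change |
|---|---|---|---|---|
| 25 | 92% | 84% | 52% | 79% |
| 20 | 88% | 85% | 60% | 69% |

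For n = 25 and c = 0.4: 0.9999 × 0.516 = 0.516. The power of the between-arm test does not depend on c.

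**The case against.** The strongest reply is that this is silence in a condensed article. A paired t test is correct for within-arm change, the section does not call its list exhaustive, the comparative intent is plain elsewhere, and a fuller protocol or SAP may name the between-arm test. Part of this stands: the intent is not in doubt and the paired test need not be deleted. But the article is not silent on the 12-week change. It assigns that variable a test, confines the unpaired tests to baseline, and so fixes an analysis that does not match its outcomes.

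The second reply is that the error rates assume a decision rule the article never states, with nearly all inputs assumed. That is fair. Nothing says the two p values will be compared, and the shared change could be negligible. For the vildagliptin-only pattern the excess is small up to about 0.1 SD. At c = 0 that pattern even detects a 0.8 SD difference more often (92%) than the between-arm test (79%). That advantage comes only from assuming that nothing else moves the glibenclamide arm. Even then, exactly one arm is significant in 9.5% of trials with identical arms, so comparing two p values is not a 5% test of the difference at any c.

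Third, an unpaired t test on the change would also close the gap. That is true: its type I error matches that of ANCOVA, and ANCOVA is a preference for using the baseline value.

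**Conclusion.** The concern holds. The named analysis of 12-week change does not test either stated outcome, and it yields no estimate, interval or p value for vildagliptin versus glibenclamide. That conclusion comes from the text alone and rests on no assumed number.

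The size of the damage from judging the drugs by the two paired results depends on the unknown shared change. With 25 per arm and no difference between drugs, a false vildagliptin-only result arises in 2.4% of trials with no shared change, 6.4% at 0.1 SD, 13% at 0.2 SD and 25% at 0.4 SD. These figures assume normal changes and that side-by-side reading. The RAS blocker carries no weight in the conclusion. The plan should be changed: the correction is small, and without it the trial's question has no stated analysis.

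**What to change.** In Statistics, replace the paired t test as the analysis of the two outcomes with wording to this effect: *RHI and central blood pressure at 12 weeks will each be compared between arms by ANCOVA, with treatment and the baseline value as covariates; the adjusted difference will be reported with its 95% CI. Within-arm paired changes are descriptive and are not evidence of a drug effect or of a difference between the drugs.* An unpaired t test on the change from baseline is an acceptable minimum.

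Cost: one degree of freedom for the baseline value. Residual degrees of freedom are 50 − 3 = 47 or 40 − 3 = 37, against 48 or 38 for an unpaired t test. No new data are needed, since Table 2 schedules both measurements at Visits 1 and 3, and the named SPSS version fits the model.

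The planned size remains usable. Taking SD 0.3 as the SD of change, an unpaired between-arm test has 80% power for 0.809 × 0.3 = 0.24 RHI units with 25 per arm, and 0.909 × 0.3 = 0.27 with 20 per arm.

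### The only test named for the 12-week change is a within-arm paired t test, although the outcomes and the sample size are between-arm

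*Protocol article*

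**What the plan says.** Under Outcomes and outcome adjudication, the protocol article gives two outcomes, both comparative: "Change in the RHI from baseline after 12 weeks of vildagliptin vs. glibenclamide treatment" and "Change in the central blood pressure from baseline to after 12 weeks of vildagliptin vs. glibenclamide treatment". Under Sample size and power calculations, the target is also comparative: "considering a 30 % change in the RHI between treatment groups as clinically relevant".

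The Statistics section then allots tests by purpose. For group comparison: "Differences between the both groups at baseline will be evaluated by unpaired" t test or Mann–Whitney test. For the outcome itself: "The change from baseline to 12-weeks follow-up in the both groups will be evaluated using the paired" t test. Chi square or Fisher's exact test is for categorical variables, and a Pearson correlation relates HbA1c to RHI and AIx. No test is named that compares the two arms on the change in RHI or in central blood pressure.

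Two treatments are common to both arms. Under Randomization and follow-up: "Renin-angiotensin system blockers will be prescribed to all subjects at the screening visit and all other antihypertensive drugs will be maintained". Metformin is also dosed to glycaemic control in each arm; for the first, "Group 1 will receive vildagliptin (100 mg/day b.i.d.) added-on to metformin (500–2550 mg/day according to glycemic control"). Table 2 places screening at week −1 and the vascular baseline at Visit 1, week 1.

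**The concern.** A paired t test compares two times in the same patients, so applied to two independent arms it can only mean one test per arm. Each test asks whether that arm changed. Neither asks whether the arms changed by different amounts, which is what the outcome definitions ask.

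The usual way to bridge that gap is to set one p-value beside the other and read significance in one arm only as a difference between drugs. That is not a test of the difference, and its error rate is not held at 5 % when both arms move together.

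A joint movement is plausible here. If a blocker is new to the patient at screening, any effect still developing after Visit 1 falls inside the 12-week change in both arms. It bears on central blood pressure as well as RHI. Metformin is a second possible source, since Table 1 has no criterion for a stable prior dose. How many patients already take a blocker, and whether metformin doses move after baseline, is not stated.

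**Working it through.** **The plan's own figure.** The protocol states 21 subjects for a 30 % change with SD 0.3, 80 % power and alpha 0.05. No baseline RHI is given, so this cannot be reproduced from its inputs. If 30 % is read as 0.30 RHI units, the two-sample normal formula gives n per arm = 2 × (1.960 + 0.842)² × (0.3/0.3)² = 15.7, so 16 per arm or 32 in total. That is a separate matter, and nothing below depends on it.

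**Inputs**
- Completers per arm: 25 × (1 − 0.20) = 20 (sample size section).
- SD of change: 0.3 if the stated SD is that of the change. If it is the SD of a single RHI reading and the two readings are uncorrelated (assumed), it is 0.3 × √2 = 0.424. The protocol does not say which.
- True difference between drugs: 0 (null case).
- Shared rise in RHI after baseline: 0, 0.05, 0.10 or 0.15. These values are assumed.

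**Within-arm paired test.** Standard error = SD/√20 = 0.0671 (SD 0.3) or 0.0949 (SD 0.424). The probability p of significant improvement is the upper-tail rejection rate of the two-sided 5 % t test with 19 df (critical value 2.093) and noncentrality shift/SE. For example, 0.10/0.0671 = 1.49 gives p = 0.293.

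**One arm significant, the other not.** The arms are independent with the same shift, so P(vildagliptin significant, glibenclamide not) = p(1 − p). For p = 0.293 this is 0.293 × 0.707 = 0.207.

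| Shared rise | p, SD 0.3 | p(1−p), SD 0.3 | p, SD 0.424 | p(1−p), SD 0.424 | Between-arm test, false claim for vildagliptin |
|---|---|---|---|---|---|
| 0 | 2.5 % | 2.4 % | 2.5 % | 2.4 % | 2.5 % |
| 0.05 | 11 % | 9 % | 7 % | 7 % | 2.5 % |
| 0.10 | 29 % | 21 % | 17 % | 14 % | 2.5 % |
| 0.15 | 56 % | 25 % | 32 % | 22 % | 2.5 % |

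The product p(1 − p) cannot exceed 25 %. It reaches that at p = 0.5, a shared rise of about 0.14 (SD 0.3) or 0.20 (SD 0.424). The between-arm column is constant because an equal shift cancels in the difference. Simulation with SD of change 0.3 gave a two-sided rejection rate of about 5 % for every shared shift from 0 to 0.3.

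**Power of a between-arm test, 20 per arm, 38 df.** SE of the difference = SD × √(2/20) = 0.0949 or 0.1342.
- Difference 0.30 × 1.68 = 0.504, taking the protocol's dysfunction cut-off of 1.68 as an assumed baseline: over 99 % (SD 0.3), about 96 % (SD 0.424).
- Difference 0.30, if 30 % is read as an absolute amount: 87 % and 59 %.
- Difference needed for 80 % power: 0.27 and 0.39.

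**The case against.** The strongest reply is that the article is condensed and its list of tests is not exhaustive. It asks for confirmation that the groups are similar on 12-week HbA1c targets without naming a test for that, so it foresees some between-arm comparison after baseline. Every statement of the aim is comparative, and nowhere does it say that the conclusion will rest on paired tests or on two p-values side by side. On that view the between-arm test has simply been left to a fuller document.

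Part of this stands. The protocol states no rule for reading the paired tests, so a false claim is a possibility it leaves open, not one it prescribes. But this is not a pure omission: the section names a test for the very quantity that defines the outcome, that test does not answer the question, and the unpaired tests are attached to baseline.

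It is also fair that no passage establishes or sizes a shared change. Blockers are prescribed before the vascular baseline, so some of their effect may be over by then. With no shared change, the one-arm-only pattern is no more frequent (2.4 %) than a false between-arm result. A shared change would also tend to appear in the glibenclamide arm, though no named test subtracts it. These points limit the illustration, but the mismatch between outcome and test needs no shared change.

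Finally, an unpaired t test of the changes would also close the gap. ANCOVA is the preferred form, not the only valid one.

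**Conclusion.** The concern holds. The named test for the 12-week change does not match the between-arm outcomes or the between-arm sample size, and this follows from the text alone.

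The size of the harm is conditional. With no drug difference and a shared RHI rise of 0.05 to 0.15, significance in the vildagliptin arm only would occur in 9 % to 25 % of trials at SD of change 0.3, or 7 % to 22 % at SD 0.424. A between-arm test gives 2.5 % in that direction. The figures assume 20 completers per arm, normally distributed changes and an equal shift in both arms. Neither the shift nor the SD of change is given in the protocol. This should be corrected before the data are analysed.

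**What to change.** In the Statistics section, name the between-arm comparison as the analysis on which the conclusion rests: ANCOVA of 12-week RHI on treatment group and baseline RHI, reporting the adjusted difference with its 95 % CI, two-sided at 0.05. Use the same model for central blood pressure. Label the within-arm paired t tests descriptive, and state that significance in one arm and not in the other will not be read as a difference between drugs.

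The cost is one model per outcome in the software already named. No visit, measurement or entry criterion changes, and patients already recruited are unaffected. The drawback is that the claim may be less favourable than two paired tests would suggest. Power is ample if the target difference is near 0.50. It is only 59 % if the target is 0.30 and the SD of change is 0.424, so the intended absolute difference should be stated alongside.
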